## 2) OBJECTIVES

*The primary objective* of this study is to evaluate effects of gamification and format of survey administration on participant retention, compliance, and engagement in a 6-month longitudinal study. The study will be structured as a siteless trial, in which brief (2-10 min) surveys will be administered remotely once per week in paper or electronic format.

To evaluate the primary objective, each participant will be assigned to one of four Arms, each consisting of two cohorts which will be recruited in sequence. Participants in each arm receive the surveys in a different format during the study (see table below). Participants in the cohorts will receive the same total compensation but on a different schedule. After enrolling approximately 50 participants each into the rapid payment cohorts (once every two weeks) of arms A, B, C, and D, or approximately 200 participants total, enrollment into the delayed payment cohorts (lump sum after 6 months) will begin.

| Arm   | Format of survey administration      | Gamified format?                                                                      | N (Approximate) | Payment Schedule                             |
|-------|--------------------------------------|---------------------------------------------------------------------------------------|-----------------|----------------------------------------------|
| Arm A | Electronic: Smartphone app           | Yes (opportunity to earn points, create custom avatar, track study progress on a map) | 50              | \$5 per completed survey, paid every 2 weeks |
|       |                                      |                                                                                       | 50              | \$5 per completed survey paid at 6 months    |
| Arm B | Electronic: Datacubed Health website | No                                                                                    | 50              | \$5 per completed survey, paid every 2 weeks |
|       |                                      |                                                                                       | 50              | \$5 per completed survey paid at 6 months    |
| Arm C | Non-electronic: Paper                | No                                                                                    | 50              | \$5 per completed survey, paid every 2 weeks |
|       |                                      |                                                                                       | 50              | \$5 per completed survey paid at 6 months    |
| Arm D | Electronic: Third-Party website      | No                                                                                    | 50              | \$5 per completed survey, paid every 2 weeks |
|       |                                      |                                                                                       | 50              | \$5 per completed survey paid at 6 months    |

*The secondary objective* of the study is to assess the effect of gamification on participant satisfaction when performing cognitive tasks, as opposed to surveys. Participants who complete any of the initial 6-month cohorts will be recontacted and asked if they would like to continue into an optional, two-week follow-up period. Up to 400 participants will be recruited for this objective. Participants will then be re-randomized in the follow-up period. Participants will be

assigned (1:1) to one of two Arms, E and F. Arm E will examine participant satisfaction with non-gamified, web-based cognitive tasks. Arm F will examine participant satisfaction with gamified, app-based cognitive tasks. Satisfaction will be assessed using a standard, validated instrument, the Technology Acceptance Model (TAM) questionnaire delivered by web or app. Participants will receive \$5 for each completed task or survey after the two-week follow-up period is complete, or up to \$30 in compensation.

| Arm   | Format of task administration | Gamified format?                                                                      | N (Approximate) |
|-------|-------------------------------|---------------------------------------------------------------------------------------|-----------------|
| Arm E | Electronic: Smartphone app    | Yes (opportunity to earn points, create custom avatar, track study progress on a map) | Up to 200       |
| Arm F | Electronic: website           | No (interactive, web-based tasks)                                                     | Up to 200       |

The specific aims of the study are:

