**Aim 3: Test whether the format of survey administration influences the self-reported usability of the survey format**

Hypothesis: There will be a main effect of the format of survey administration on self-reported usability of the survey format. Usability will be derived from a self-report usability survey that assesses the ease of use and pleasantness of the survey format; an overall measure of usability as well as different factors of usability will be derived from the survey responses.

Administration on paper will result in the lowest usability, and electronic administration on the gamified mobile app will result in the highest usability. Electronic administration on the non-gamified websites will result in intermediate usability, with use of Datacubed Health's website resulting in usability equivalent to or superior to a third-party website (i.e., paper < third-party website < Datacubed Health website < mobile app).

**Aim 4: Test whether payment schedule influences retention and compliance differently by format of instrument administration.**

Hypothesis: There will be a significant difference in retention and compliance between participants who receive biweekly payments and participants who receive one payment, adding up to the same amount, at study end. All participants will receive \$5.00 for each completed survey. Participants who receive payment at study end will show reduced retention and compliance, and this will vary by format of survey administration (mobile vs. Datacubed web vs. third-party web vs. paper).

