#### **6) STUDY-WIDE RECRUITMENT METHODS**

Potential participants are expected to be recruited over the course of one year, starting at the end of Q3 2020 or start of Q4 2020. An advertisement in the Metro newspaper will be placed to recruit potential participants; both a print ad (in the physical print Metro newspaper in New York City) and an electronic ad (on Metro's website) will be placed. Electronic ads will be placed in

the New York City page of the Craigslist website, specifically in the ‘Volunteers’ section. Electronic ads will be posted on Facebook and Instagram, and links will be posted on Facebook and Reddit groups that include primarily adult participants located in the United States. The study will also be posted to online participant recruitment platforms including, but not limited to, User Interviews and Autocruitment. The print Metro newspaper is free and accessible from distribution racks placed inside 100 New York City subway stations; the websites and social media platforms are free and accessible to anyone with an internet connection.

The source of participants will be people who self-report living in the United States who meet one of the following criteria;

- Read the physical print Metro newspaper or the Metro website
- Use Craigslist, Instagram, Facebook, or Reddit.
- Are part of third-party websites (e.g., User Interviews, Autocruitment) which function to connect participants with user research studies.

A copy of the ad (print and online) is included as an attachment in this application. The ads include the following information:

- Description of Datacubed Health
- Description of the study design + objectives
- Eligibility requirements for study participation
- Study participation requirements: completion of approximately one survey per week
- Compensation for study participation: \$5 for each survey or task completed
- Contact information for Datacubed Health (link to website)

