## 9) STUDY DESIGN AND PROCEDURES

### Arms A-D

This study will employ at initial recruitment a between-subjects design with four, independent arms, divided into two sequential cohorts.

Each participant will first complete the informed consent process (see Section 29). Upon receipt of the signed consent (signature captured digitally), Datacubed Health will assign the participant

to one of 4 groups; group assignment will determine the medium through which the surveys will be administered -- gamified mobile app (Arm A), web browser (Arm B & Arm D), or paper (Arm C). Approximately 100 participants are expected to be enrolled into each group.

Group assignment will be done sequentially by date and time of consent signature – i.e., the first participant who signs consent will be assigned to Arm A; the second participant, to Arm B; the third participant, to Arm C; the fourth participant, to Arm D; the fifth participant, to Arm A; the sixth participant, to Arm B; etc. The first cohort of participants recruited into each arm will receive compensation every two weeks based on how many instruments they complete (\$5/instrument). The second cohort of participants recruited into each arm will receive a single payment at the conclusion of the 6-month arm. Compensation will be the same, \$5/instrument, but delivered as a single lump sum payment after completion. The maximum, total compensation possible in the initial 6-month study period will be \$130.

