## **Aim 4: Test whether payment schedule influences retention and compliance.**

To test whether payment schedule influences retention and compliance (Aim 4), we will perform a two-way ANOVA to compare overall retention and compliance between groups (Arms A vs. B vs. C vs. D) and payment schedule (payment biweekly vs. payment at study end). A significant interaction effect is expected, such that differences in retention and compliance between arms will be more pronounced among participants receiving one payment at the end of the study.

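### Payment schedule follows enrolment order, so the Aim 4 payment main effect is a non-randomised comparison of sequential cohorts that cannot be separated from calendar time

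*Protocol*

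**What the plan says.** Section 2 of the protocol describes four arms, "each consisting of two cohorts which will be recruited in sequence". The switch between payment schedules is a matter of enrolment count: once the biweekly cohorts hold about 50 per arm, "or approximately 200 participants total, enrollment into the delayed payment cohorts (lump sum after 6 months) will begin".

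Section 9 (Arms A-D) repeats the rule: "The first cohort of participants recruited into each arm will receive compensation every two weeks based on how many instruments they complete", and then "The second cohort of participants recruited into each arm will receive a single payment at the conclusion of the 6-month arm". The later payment paragraph of Section 9, and Section 21, say the same.

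Format is handled differently. According to Section 9, "Group assignment will be done sequentially by date and time of consent signature", rotating A, B, C, D, so all four formats enrol side by side within each payment cohort.

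The Aim 4 hypothesis in Section 2 reads: "There will be a significant difference in retention and compliance between participants who receive biweekly payments and participants who receive one payment". It predicts lower retention and compliance with payment at study end, to a degree that varies by format. In Section 11, under Aim 4, "we will perform a two-way ANOVA to compare overall retention and compliance between groups" and payment schedule. No period term is named, and the one result predicted there is an interaction.

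Section 6 says participants are "expected to be recruited over the course of one year", through a newspaper, classified advertisements, social media and an open-ended list of recruitment platforms.

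**The concern.** Aim 4 asks whether payment schedule influences retention and compliance, which is a causal question about two of the primary outcomes in Section 8. Yet nobody enrolling on a given day could have received either schedule. Everyone in the first half of enrolment is paid every two weeks and everyone in the second half is paid once, at the end. No overlap between the cohorts and no concurrent control is described.

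The cohorts may therefore also differ in season, recruitment source mix, app or website version, mail conditions, and how keen early responders are compared with late ones. The planned ANOVA would book any such difference to payment. If early responders happened to be the more engaged, the bias would imitate the hypothesised effect.

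At stake is the first half of the Aim 4 hypothesis. Because the defect lies in how payment is allocated, a statistical analysis plan could not repair it.

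**Working it through.** **Inputs from the protocol.** Four arms, two cohorts per arm, about 50 per cell (Section 2 table); up to 400 in total (Section 5); payment switched by enrolment order (Sections 2, 9 and 21); arm rotated by consent time (Section 9); two-way ANOVA of arm by payment (Section 11).

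**Assumptions.** The protocol gives no alpha, SD or effect size for Aim 4. I take two-sided 5% and SD = 1, and let d be an assumed drift between the two enrolment periods, in SD units.

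**Step 1: the plan's own figure.** 4 × 50 = 200 per payment cohort and 2 × 200 = 400, which agrees with Section 5.

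**Step 2: aliasing.** A model with an intercept, three arm indicators and one payment indicator has 5 columns and rank 5. Adding an indicator for the second enrolment period gives 6 columns, but the rank stays at 5: the period column equals the payment column. A linear enrolment-order covariate can be fitted instead, but it correlates 0.87 with payment. The variance inflation is 1/(1 − 0.866²) ≈ 4, and the adjusted estimate then depends on the trend really being linear.

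**Step 3: size of the distortion when payment has no effect.** The standard error of the cohort difference is √(1/200 + 1/200) = 0.10 SD. The chance of a significant payment term is P(|Z + d/0.10| > 1.96). I checked this against 4,000 simulated trials per row, using the planned ANOVA with 50 per cell.

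| Assumed drift d (SD) | Formula | Simulated, planned design | Simulated, payment randomised concurrently |
|---|---|---|---|
| 0 | 5% | 4.7% | 5.5% |
| 0.1 | 17% | 16.4% | 5.2% |
| 0.2 | 52% | 50.3% | 4.9% |
| 0.3 | 85% | 83.9% | 4.6% |

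**Step 4: the interaction.** In the same simulations of the planned design, with a drift common to all four formats, the arm-by-payment test rejected in 4.6% to 5.2% of trials. A common drift cancels because the formats run side by side within each cohort. The interaction is biased only if the drift differs by format.

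**Step 5: Aims 1 to 3.** Format is rotated within each cohort, so every format draws about half its participants from each period. Payment order does not confound the format comparisons.

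**The case against.** The strongest defence is that the damage is narrow. The primary objective concerns gamification and format, and payment enters only through Aim 4. The Aim 4 heading in Section 2 asks whether payment acts differently by format, and Section 11 predicts only an interaction, which is the part that a common drift leaves intact. All of that stands. It does not save the main effect, because the Aim 4 hypothesis in Section 2 also predicts a plain difference between schedules, and the Aim 4 heading in Section 11 asks whether payment has an influence.

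Two stronger readings are tempting. A reader might infer that payment is equally inseparable from recruitment source, or that the cohorts are known to differ in source, app version or mail service. The documents do not support this. Only calendar time is aliased by design. Section 6 lists the channels without saying that they change between cohorts, and no passage reports a change of app, website or mail. These are risks. A reader might also infer that the whole trial is compromised, which Steps 4 and 5 contradict.

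It is also fair to say that nothing in the protocol indicates how large any drift would be. The percentages show how sensitive the test is, and do not forecast what this trial will find. Section 9 does plan to examine whether demographics are associated with the outcomes. That is partial handling of case mix, but it does nothing about calendar time.

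**Conclusion.** The concern holds for the Aim 4 payment main effect, which is fully aliased with enrolment period and is therefore a non-randomised comparison of successive cohorts. Under the assumptions in the working, a drift of 0.1 SD raises the false-positive rate from 5% to about 17%, 0.2 SD to about 52%, and 0.3 SD to about 85%. The aliasing itself rests on no assumption; it follows from the allocation rule.

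The format-by-payment interaction remains interpretable provided that the period effect is the same in every format, an assumption the protocol should state. A change confined to one format, such as slower mail or a new app release, would break it, but the documents report no such change.

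**What to change.** **Preferred.** Allocate payment schedule at random and concurrently within format from the first enrolment, for example in blocks of eight that contain each format-by-payment cell once. This gives eight cells of about 50, with the same 400 participants and the same $5 per survey. In the simulations it kept the false-positive rate of the payment term near 5% whatever the common drift. It needs a change to the protocol and consent wording and one allocation list. Section 9 already informs participants of group and payment scheme after consent, so no new step is added. The small downside is running two payment calendars in parallel.

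**If the biweekly cohort is already full.** Describe the payment main effect as a non-randomised sequential-cohort comparison and make no causal claim for it. Centre Aim 4 on the format-by-payment interaction and state the common-trend assumption. Adjust for the demographics that Section 9 collects. Adjust for recruitment source only if it is recorded: Section 9 does not list it among the data collected, so it would have to be added. This route changes wording and analysis only, but it leaves the main effect unidentified.

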**Aim 1: Test whether electronic administration influences participant retention and compliance**

Hypothesis: There will be a significant difference in retention and compliance between paper and electronic (web) administration of surveys. Retention will be measured by the number of days from the first assigned instrument to the date of the last fully completed instrument and compliance will be measured by the number of fully completed instruments. Electronic administration will improve retention and compliance, such that administration on paper will have lower retention and compliance compared to electronic administration on the non-gamified websites (Datacubed Health website and third-party website).

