## **7) STUDY TIMELINES**

Each participant will be asked to complete surveys for six months after enrollment. Over the course of that six-month period, they will receive roughly one survey each week either by mail, within the smartphone app, through the Datacubed Health website, or through a third-party

website. Each survey will last no longer than 10 minutes, but most will be shorter (~3 minutes). A subset of participants who complete the initial six-month period will be given the option to continue into a two-week follow-up period, during which they will complete up to 6 more activities (cognitive tasks and usability/TAM surveys).

We plan to enroll all participants in the study within one year. We plan to complete primary analyses of the study data within two years.

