## 8) STUDY ENDPOINTS

The primary outcomes of interest are measures of *retention*, *compliance*, and *usability*.

- *Retention* will be defined as the amount of time participants remain active in the study. Specifically, the primary retention measure will be the number of days between the participant's first assigned study instrument and the date of the last assigned study instrument that they complete.
- *Compliance* will be defined as the number of instruments that the participant fully completes (i.e. responses for all required items) over the course of the study.
- *Usability* will be derived from a survey-based measure that assesses the perceived ease of use and pleasantness of the survey format (see separate attachment). The mean score across items of the survey measure will be used as the primary usability outcome measure of the overall usability of the survey format.

The exploratory outcome measures of interest are measures of *churn*, *engagement*, *activities*, and *routine*:

- *Churn* will be defined as missing more than 25% of assigned instruments within a study phase. Study phases will be defined at the 1 month, 3 month, and 6 month milestones.
- *Engagement* will be assessed based on participant behaviors while using the gamified mobile app (Arm A), and will include the number of clicks on the avatar, number of changes made to the avatar, number of gem store purchases, and the total amount of time spent on the app.
- *Activities* will be defined by classification of clusters of spatiotemporal geolocation data (Arm A).
- *Routine* will be defined by a directed graph model of the *activities*; characteristics will be explored using graph theoretic measures (Arm A).

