Each participant will be informed immediately of their group assignment and compensation scheme. Participants who are assigned to the mobile app group will receive additional instructions on how to download and log into the app. Participants who are assigned to the Datacubed Health website group will receive an email with instructions and a link to log into the Datacubed Health web portal. Participants who are assigned to the third-party website (Qualtrics) will be informed that they should expect to receive an email with a custom link to complete surveys each week. The third-party website will not be provided with any participant information, including email addresses. Subjects will only be identified to the third-party website with unique, randomly generated alphanumeric IDs. A script hosted by Datacubed Health will link these IDs to participant email addresses, internally. A master list of alphanumeric subject IDs and participant email addresses will be visible only to study administrative staff at Datacubed Health. Participants who are assigned to the paper group will be informed that they should expect to start receiving their surveys by mail each week.

Participants in all groups will be assigned the same set of study instruments, in the same order. See separate attachments for a listing and full text of all planned survey instruments. Each instrument will take no more than 10 minutes to complete (including embedded instructions), but most will be substantially shorter (2-3 minutes).

Participants in the gamified mobile app condition must log into the mobile app and will see a rich user interface - this includes a customizable avatar, progress-tracking maps that are gradually revealed as study activities are completed, points earned by completing study activities that can be redeemed for virtual avatar accessories (e.g. a hat or sunglasses), and other appealingly designed features (e.g. animated confetti displayed when study activities are completed). Participants in the non-gamified web conditions (Datacubed Health and third-party) must log into the respective web platform and will simply see a scrollable list of available study activities. Participants in the paper condition will be mailed paper surveys, which they must return to the study team through mail using pre-addressed and stamped envelopes. Screenshots illustrating examples of each study condition are provided as a separate attachment.

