Certain demographic data, such as age (month and year of birth only; all subjects are under 90), gender, sex, ethnicity, education level, employment status, annual income level, and type of smartphone, will be collected from all participants. These data will be analyzed to see if they are associated with any differences in retention, compliance, and engagement. For security, these data will be encrypted and stored in separate files, which can only be referenced through the anonymous subject ID that is assigned to each participant for the study.

Survey data, including survey responses, number of surveys completed, and dates of survey completed will be collected for all participants. These data will be used to evaluate the study endpoints of participant retention, compliance, and usability.

In addition to the aforementioned data types, for the group assigned to the gamified mobile app, several types of data provided by the phone operating system will be collected:

- **Passive data:** These types of data will be collected even when the participant is not actively using the app. Specifically, the app will record information about the participant's

phone battery percentage, geolocation, number of steps taken, apps installed on the phone, and phone screen on/off times. Participants will be fully informed during the consent process that the app will collect such data. They will be able to disable collection of location and step count data at any time by restricting the app permissions via the phone operating system; Android phone owners will also be able to restrict permissions for data collection on screen time.

- Geolocation is the collection of precise geographical location (latitude and longitude) of a device through a mixture of GPS and WiFi signals. This technology is used by many other apps that provide services based on a user's location, such as navigation, rideshare, banking, dating, and fitness apps. When location permissions are allowed, location data is sent to the app every few minutes. In this study, geolocation data will only be used to develop a data-driven model of participants' daily routines. This model will then be compared with self-reported measures of daily activity to see if geolocation data can serve as a measure of activity and routine. Datacubed Health will not share geolocation data with any other external parties and will destroy this data at the end of the study.

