### **Aim 1: Test whether electronic administration influences participant retention and compliance**

To test whether electronic administration influences participant retention and compliance, we will perform a one-way analysis of variance (ANOVA) with Dunnett's test for multiple comparisons to assess retention and compliance between the groups receiving paper-based administration of surveys and the two groups receiving electronic administration on the non-gamified websites. Non-parametric alternatives (e.g., Kruskal-Wallis test) may be used in place of ANOVA if the data significantly violate the assumptions for ANOVA. This approach will eliminate the potential confounding effect of gamification on the outcome measures by excluding the group receiving electronic administration of the gamified mobile app.

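### Retention has two end-date wordings; on the completion-date reading, paper Arm C can be credited with mail time, which biases Aim 1 against its own hypothesis

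*Protocol*

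**What the plan says.** Retention is one of the primary outcomes in Section 8, and it is worded in two places.

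- Section 2, Aim 1: "Retention will be measured by the number of days from the first assigned instrument to the date of the last fully completed instrument". The clock starts on an assignment date and stops on a completion date.
- Section 8: the clock starts at the first assigned instrument and stops on "the date of the last assigned study instrument that they complete". The date can belong to the assignment or to the completion. This wording also drops the word fully.

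The opening of the data analysis plan in Section 11 points to Section 8 for how each measure is calculated. Section 9 lists the data kept: "dates of survey completed will be collected for all participants", followed by "These data will be used to evaluate the study endpoints of participant retention, compliance, and usability".

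On delivery, Section 7 says of participants that "they will receive roughly one survey each week either by mail, within the smartphone app" or through one of two websites. Section 9 adds: "Participants in the paper condition will be mailed paper surveys, which they must return to the study team through mail". The protocol does not say what counts as the assignment date of a paper survey, or whether a paper survey is dated when filled in, postmarked or received.

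Aim 1 compares paper with the two websites by one-way ANOVA with Dunnett's test. If assumptions are significantly violated, "Non-parametric alternatives (e.g., Kruskal-Wallis test) may be used in place of ANOVA".

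**The concern.** If the clock starts at assignment and stops at completion, the time taken to receive, answer and possibly return the last survey is scored as time retained. A website survey is available once it is assigned. A paper survey must travel first. Outbound mail counts if assignment means the mailing date or the common weekly schedule date. Return mail counts if receipt is what gets logged.

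Format is the factor that Aim 1 tests, so this lag is fully confounded with the comparison. It works against the hypothesis that paper retains worse, and could hide or shrink a real advantage of electronic administration. A rank test is especially exposed: most finishers share the same last instrument, so their ranks depend on how many days that one answer took.

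**Working it through.** The protocol states no standard deviation, effect size, power or transit time for retention, so there is no figure to reproduce.

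**Inputs from the protocol.** About 100 per arm (Section 9). $130 / $5 = 26 weekly instruments (Section 21), so assignments fall on days 0 to 25 × 7 = 175. Dropout of up to 30% is a background figure (Section 3).

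**Assumptions.** Two-sided alpha 0.05. Answers come 0-6 days after the survey reaches the participant, in both formats. Extra paper lag is 1-2, 3-5 or 6-10 days (means 1.5, 4, 8). A fraction p drops out, with the last instrument uniform over weeks 1-25 (days 0-168, mean 84); the rest complete instrument 26.

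**1. Size of the shift.** Completion-date retention = assigned day of last completed instrument + delay to completion. With equal dropout, the expected paper minus web difference is the extra lag, added once and not accumulated.

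**2. Mean and SD of the assigned day.** Mean = 175(1 − p) + 84p = 175 − 91p. Variance = p(1 − p) × 91² + p × 49 × (25² − 1)/12.
- p = 0.30: 1,739 + 764 = 2,503; SD 50.0.
- p = 0.40: 1,987 + 1,019 = about 3,007; SD 54.8.

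The 0-6 day answering spread adds a variance of only 4 and is ignored here.

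**3. Mean-based test, 30% dropout in both arms.** SE = √(2 × 2,503/100) = 7.08. P(paper significantly better) = Φ(lag/7.08 − 1.96).

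**4. Rank test, same setting.** Let q be the chance that a paper finisher ranks above a web finisher, ties counted half. For a 4-day lag, of the 49 pairs of answer days paper is later in 43 and tied in 3, so q = (43 + 1.5)/49 = 0.908. For 8 days q = 1. For 1 and 2 days q = 31/49 and 36.5/49, average 0.689. Then θ = 0.49q + 0.21 + 0.045, with null SE = √(201/(12 × 100 × 100)) = 0.0409.

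| Mean lag (days) | Mean test favours paper | θ | Rank test favours paper |
|---|---|---|---|
| 1.5 | 4% | 0.593 | 62% |
| 4 | 8% | 0.700 | 99.8% |
| 8 | 20% | 0.745 | >99.9% |

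Simulation (Welch t and Mann-Whitney) agrees: t-test about 4%, 7-8% and 19-22%. The rank figures fall when instruments are missed. At 80% completion they are about 35% for 1-2 days and 95% for 3-5 days; at 60% completion, about 73% for 3-5 days.

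**5. Real difference: 40% paper, 30% web dropout.** True web advantage = 91 × 0.10 = 9.1 days. It becomes 9.1 − 4 = 5.1 or 9.1 − 8 = 1.1 days. SE = √((2,503 + 3,007)/100) = 7.42.
- Mean test significantly favours paper: Φ(−1.96 − 5.1/7.42) = 0.4%; Φ(−1.96 − 1.1/7.42) = 1.8%.
- Rank test, θ = 0.42q + 0.18 + 0.06: 0.529, 0.621 and 0.660, which give about 11%, 84% and 97% for mean lags of 1.5, 4 and 8 days.
- With 3-5 days' mail and 90%, 80% or 60% of instruments completed, simulation gives 66%, 50% and 19%. For 1-2 days with some missed instruments it is about 4%.

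**6. A second model with the tests named for Aim 1.** Constant weekly dropout hazard, three arms of 100, 90% completion while active, Dunnett critical value 2.22, 1,500 trials per scenario, equal dropout. At 30% dropout (SD about 51), lags of 3, 7, 10 and 14 days make Dunnett favour paper in 7%, 17%, 30% and 54% of trials. Kruskal-Wallis is significant with paper highest in 50%, 73%, 85% and 96%. Across those lags, 10% dropout gives Dunnett 12-91% and Kruskal-Wallis 62% to over 99%; 50% dropout gives 6-40% and 47-89%.

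**7. Scored by assigned date, equal dropout.** In the second model the mean difference stays between −0.23 and +0.27 days and both tests reject in about 4-6% of trials. The bias disappears.

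**The case against.** The strongest reply is that Section 8 governs, because the analysis plan points there, and that its wording can be read as the assigned date. On that reading there is no bias, and the Aim 1 sentence is loose prose. This stands in part: the completion-date reading is not settled. But Section 8 does not say which date it means, and Aim 1 does. The data list in Section 9 leans towards completion dates without deciding the matter, since it covers three endpoints at once. A conflict in the wording of a primary outcome remains.

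Second, outbound transit is an assumption, because surveys might be mailed to arrive in the target week, and return transit depends on how receipt is handled. This also stands. Such dating rules commonly sit in a statistical analysis plan or data-management document that is not shown, so their absence is not the point raised here.

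Third, the large percentages belong to a fallback that is only permitted, not planned. True, although retention scores bunched near day 175 make its use plausible. The fallback figures also depend heavily on transit time and missed instruments, so no single one should be quoted as the answer.

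A reader might infer that every retained paper participant outscores an equally retained web participant. That is too strong: the assumed 0-6 day answering spread overlaps a 3-5 day lag, so the shift holds only on average.

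**Conclusion.** The point holds as a conflict in a primary outcome definition that should be fixed. On the completion-date reading, Arm C gains on average about its extra lag in days, opposite to the Aim 1 hypothesis. With equal 30% dropout and 3-10 days' lag, the t-test favours paper in about 7-22% of trials and the rank test in about 95-100% (lower if completion falls well below 80%). For 1-2 days the figures are about 4% and 35-60%.

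A reader might infer that Aim 1 will reverse. The documents do not support that. Under the planned mean-based analysis with a real web advantage, the main effect is attenuation, from about 9 days to about 5 or 1, with significant reversal in 2% of trials or fewer. Under the rank fallback the share favouring paper runs from about 4% to 97%, depending on lag and missed instruments.

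Scope is limited. Compliance is a count and gains no days, and Aim 2 excludes paper. The arm effect in Aim 4 uses the same retention measure and shares the problem. All sizes rest on assumed transit, dropout and completion rates; the mechanism needs only the completion-date reading and a longer lag on paper.

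**What to change.** Use one definition in Section 2 (Aim 1) and Section 8, for all arms: retention runs from the first assigned instrument to the scheduled (assigned) date or week of the last instrument that the participant fully completes, regardless of when it was answered or received. Add that returns are accepted for the same fixed period after the last assigned instrument in every arm, long enough to cover mail time, so that late post does not cut off Arm C's final surveys.

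The cost is two sentences. No new data are needed, because assignment dates follow the schedule. Day-level resolution within a week is lost.
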